### Outcome measurement

2.9

#### Primary outcome

2.9.1

**PSQI** is a validated, widely used tool for assessing sleep disorders (49). It is easy to administer and demonstrates high reliability and validity (50). The PSQI evaluates sleep quality over the previous month in individuals with organic or non-organic sleep disorders. It comprises 23 items, grouped into seven components: subjective sleep quality, sleep latency, sleep duration, habitual sleep efficiency, sleep disturbances, use of sleep medication, and daytime dysfunction. Each component is scored from 0 to 3, yielding a total PSQI score ranging from 0 to 21. A score > 7 indicates poor sleep quality, with higher scores denoting greater impairment (50).

### Secondary outcomes

2.9.2

#### ISI

2.9.2.1

This scale is used to assess the severity of insomnia and treatment outcomes over the past two weeks (51, 52). It includes five items comprising seven questions, each rated on a five-point scale (0–4). The total score ranges from 0 to 28, with clinical interpretation as follows: 0–7, no clinically significant insomnia; 8–14, subthreshold insomnia; 15–21, moderate clinical insomnia; 22–28, severe clinical insomnia.

#### Actigraphy-derived sleep data

2.9.2.2

The ActiGraph wGT3X-BT (ActiGraph LLC, USA) is a wearable device worn on the non-dominant wrist. It incorporates high-precision accelerometers, gyroscopes, and additional sensors to objectively capture limb movements. This enables the collection of sleep-related parameters, supplementing self-reported sleep diaries. Data will be analysed using the sleep module of ActiLife software version 6.13.6 (ActiGraph LLC, USA) to extract metrics such as total sleep time, sleep efficiency, total wake time, and number of awakenings after sleep onset. Numerous studies have shown strong concordance between actigraphy and polysomnography (PSG) data (53–55). For older adults with insomnia, actigraphy provides a more ecologically valid representation of habitual sleep patterns than PSG, which requires environmental modification and complex leads, thereby making it an effective tool for evaluating clinical efficacy and for follow-up assessments.

#### Sleep diary

2.9.2.3

The Consensus Sleep Diary is a standardised self-report instrument used to record daily sleep parameters, including bedtime, wake-up time, sleep latency, number of awakenings, wake time after sleep onset, use of hypnotics, and subjective sleep quality ratings (56). From these entries, sleep duration and sleep efficiency can be calculated. Sleep diaries offer insights into subjective sleep experiences and can capture behavioural patterns not readily revealed through objective measures. Their simplicity, ease of use, and capacity for repeated sampling enhance the long-term reliability of sleep assessments.

#### HADS

2.9.2.4

Developed by Zigmond AS and Snaith RP in 1983 (57), is a widely used self-report tool for assessing symptoms of anxiety and depression. It has demonstrated strong psychometric properties in Chinese populations (58–60). The HADS comprises 14 items, with two subscales: HADS-A (anxiety) and HADS-D (depression), each containing seven items. This study will employ the Chinese version revised by [name] of the Chinese University of Hong Kong (61).

#### Hypnotic medication use

2.9.2.6

Participants will document their use of hypnotic medications in sleep diaries. Upon data collection, the proportion of participants using hypnotics in both groups before and after the intervention, as well as the proportion with increased or decreased dosages, will be calculated.

#### Blinding assessment

2.9.2.7

Before trial initiation, participants will be informed that they have an equal chance of being assigned to either intervention group. Immediately following the intervention period, outcome assessors will evaluate the success of blinding by asking participants to guess their intervention allocation. Blinding efficacy will be quantified using Bang’s Blinding Index (64).

### Adverse events

2.10

Throughout the trial, adverse events (AEs) will be monitored and recorded by participants, outcome assessors, and acupuncturists using a modified acupuncture adverse event recording form. Based on the potential association with the EA or SEA intervention, all AEs will be reviewed and classified as intervention-related or non–intervention-related by the acupuncturist in consultation with relevant experts within 24 h of occurrence. Common AEs associated with EA and SEA include severe pain, subcutaneous hematoma, skin reactions, syncope, and other discomforts. Clinically significant abnormalities in vital signs or laboratory findings will also be recorded as AEs. Appropriate clinical management will be provided according to the severity of the event, and detailed records will be maintained. The incidence of AEs will be reported as the ratio of the total number of events to the total number of intervention sessions.

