### Randomisation and blinding

2.7

Participant randomisation will be conducted via a centralised, web-based system. An independent statistician, uninvolved in trial execution, will generate the allocation sequence using SAS 9.4 software, employing stratified block randomisation with two stratification factors: study site and current use of hypnotic medication. Variable block sizes (2, 4, 6, or) will be used. Following confirmation of eligibility, designated randomization personnel at each study site will input the participant’s information into the central system to obtain a unique identification number and treatment allocation. Access to this system will be restricted to randomisation personnel and data monitors; all other study staff, including outcome assessors and statisticians, will remain blinded. Randomisation personnel will only be able to view participants and allocations within their respective centre.

This trial adopts a single-blind design, with participants blinded to group allocation. Due to the nature of EA, blinding of acupuncturists is not feasible. Participants will be informed during enrolment that they have an equal probability of being assigned to either intervention group. To ensure effective blinding, sham acupuncture needles with validated manufacturing standards and prior use in clinical trials will be used for the SEA group (35–37). Participants will undergo treatment in a supine position while wearing eye masks, and all interventions will be conducted in separate rooms to minimise cross-group contamination. Blinding integrity will be assessed at week 8, after the final treatment session, by asking participants to guess their group assignment. Apart from the acupuncturists administering the intervention, all other study personnel, including outcome assessors and statisticians, will remain blinded until the trial’s conclusion, at which point routine unblinding will be performed. All research staff will undergo comprehensive training prior to trial initiation and will strictly adhere to role separation protocols across departments.

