### Intervention

2.8

Both EA and SEA groups will receive standardised sleep hygiene education in accordance with the Chinese Guidelines for the Diagnosis and Treatment of Adult Insomnia (2017) (46), which includes the following recommendations: ① Avoid consumption of stimulants such as coffee, strong tea, or tobacco within 4–6 h before bedtime; ② Refrain from alcohol use before sleep, particularly as a sedative; ③ Engage in daily moderate physical activity, avoiding intense exercise within 3–4 h before bedtime; ④ Avoid overeating or consuming difficult-to-digest foods prior to bedtime; ⑤ Minimise exposure to stimulating activities, including watching television or reading emotionally arousing material, within 1 h before sleep; ⑥ Maintain a quiet, comfortable, and appropriately lit and temperature-controlled bedroom environment; ⑦ Establish and adhere to a consistent sleep–wake schedule.

Participants in both groups will receive 24 intervention sessions (30 min each), administered three times per week on alternate days over 8 weeks. During each session, participants will lie supine, with intervention areas exposed and eye masks worn to block visual stimuli. Licensed TCM practitioners with over three years of clinical experience, all of whom have completed standardised training specific to this trial, will administer either EA or SEA based on group assignment.

Participants already using hypnotic medications at baseline may continue their prescribed regimens but must record all medication usage. Dose escalation is prohibited unless approved by a psychiatrist. Participants not taking hypnotics at baseline will not be allowed to initiate or increase hypnotic use during the study. In the event of severe insomnia symptoms, such as persistent sleeplessness over multiple nights, participants may use emergency medication—zolpidem tartrate tablets (Stilnox, 5 mg; National Medicine Permit H20181237, Sanofi Winthrop Industrie)—and must document its use. Concurrent insomnia-related treatments, including dietary supplements, Chinese herbal medicines, and CBT-I, are not permitted during the trial.

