### Data collection and management

2.11

Data collection will be conducted by assessors at each clinical site who are independent of both intervention delivery and statistical analysis. All scale-based assessments will be performed in separate rooms to ensure privacy and reduce bias. Assessors, who are blinded to the participants’ group allocation, will undergo standardised training and will provide only necessary clarifications on assessment tools, without influencing participant responses. At each assessment time point, both assessors and participants will be limited to the specific scale being administered. Participants will complete their sleep diaries and promptly submit them to the assessors. Actigraphy data will be downloaded and analysed by trained assessors using ActiLife software.

Recognising the challenges of ensuring accurate and complete self-recording of sleep diaries and actigraphy data, a comprehensive compliance strategy will be implemented. This includes in-person training at baseline on the use of sleep diaries and actigraphy devices, with reinforcement sessions at weeks 4 and 8. A robust monitoring protocol will also be in place, whereby assessors will routinely verify data completeness and accuracy, providing immediate feedback and reminders to participants as needed.

All study data will be initially documented in standardised, paper-based Case Report Forms (CRFs) and subsequently entered into a web-based Electronic Data Capture (EDC) system. Double data entry will be employed to minimise errors. Data entry personnel at each site will remain uninvolved in other trial procedures and will have access only to data from their respective centres. An independent Data and Safety Monitoring Board (DSMB) will oversee data integrity and safety. If discrepancies arise, a data supervisor will issue a query form to the responsible researcher for clarification. If required, the statistician may also initiate a query. All responses will be recorded on the query form, which will then be returned to the statistician by the trial inspector.

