
Despite its strengths, the study faces certain limitations and implementation challenges. First, due to the nature of acupuncture, a double-blind design is not feasible. To address this, we will implement Standard Operating Procedures (SOPs) for intervention delivery, standardising needling techniques and controlling practitioner-participant interactions, while ensuring strict separation between intervention, assessment, and data analysis teams. Second, the extended duration and high frequency of EA sessions, combined with requirements for participants to maintain sleep diaries and wear actigraphy devices, may affect adherence and contribute to attrition. Third, the success of the blinding procedure relies on participants’ perceptions, which may vary and influence outcomes. Future research should consider incorporating objective biomarkers or extended follow-up periods to better assess the durability and mechanism of treatment effects.

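### Section 2.10 has the unblinded acupuncturist, with unnamed experts, classify the relatedness of every adverse event, so the related/unrelated split is open to attribution that differs by arm

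*Protocol article*

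**What the plan says.** Section 2.10 (Adverse events) states the rule for causality: every AE is sorted into related or unrelated to the intervention "by the acupuncturist in consultation with relevant experts within 24 h of occurrence". The experts are not identified. The article does not say whether they are blinded or who decides if they disagree with the acupuncturist.

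The same section says that "adverse events (AEs) will be monitored and recorded by participants, outcome assessors, and acupuncturists", and it reports AE incidence as all events divided by all sessions given.

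Section 2.7 (Randomisation and blinding) says: "Due to the nature of EA, blinding of acupuncturists is not feasible". Its blinding paragraph makes the treating acupuncturists the only exception among study personnel. Section 2.8 (Intervention) confirms that these practitioners "will administer either EA or SEA based on group assignment".

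Section 2.11 (Data collection and management) says: "Data collection will be conducted by assessors at each clinical site who are independent of both intervention delivery and statistical analysis". It adds: "An independent Data and Safety Monitoring Board (DSMB) will oversee data integrity and safety". The Discussion lists, among its answers to the lack of a double blind, "ensuring strict separation between intervention, assessment, and data analysis teams".

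**The concern.** Deciding whether the intervention caused an event is an assessment. Section 2.10 gives the lead in it to the team that delivers the intervention and knows the arm. Elsewhere the protocol relies on keeping treatment and assessment apart.

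The arms differ in ways that invite different attribution of the same complaint. EA uses penetrating needles and current; the sham uses blunt needles that do not penetrate and carry no current. An acupuncturist might discount a vague discomfort after real needling as trivial or expected, or might assume that the sham cannot cause anything. These tendencies push in opposite directions, so the sign of any bias is unknown and it could not be corrected afterwards. Safety is one of the two aims in section 2.1, so any between-arm statement about intervention-related events would carry this weakness.

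**Working it through.** The point rests on no figure in the plan, so the main check is to set the sections side by side.

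**1. Who does what.**

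| Step | Who | Knows the arm? | Source |
|---|---|---|---|
| Delivers EA or sham | Acupuncturist | Yes | 2.7, 2.8 |
| Records AEs | Participant, outcome assessor, acupuncturist | No, no, yes | 2.10, 2.7 |
| Classifies relatedness | Acupuncturist, after consulting experts | Yes; experts not stated | 2.10, 2.7 |
| Oversees safety | DSMB | Not stated | 2.11 |

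The classification row is where the treatment team leads an assessment. The DSMB is given no part in it.

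**2. Does the consultation settle it?** If the experts are study personnel, the general statement in 2.7 would keep them blinded. Discussing causality with an unblinded colleague could then reveal the arm. If they are not study personnel, nothing in the article blinds them. In both cases the acupuncturist is the named classifier and no rule covers disagreement.

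**3. What does the label affect?** Write the stated incidence in one arm as E / S, with E all events and S all sessions. The planned maximum is S = 24 sessions × 107 participants = 2,568 per arm. Let E = R + U (related plus unrelated). Moving k events from R to U gives (R − k) + (U + k) = E, so E / S does not change. Only R and U separately depend on the label.

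**4. Can the bias in the split be sized?** If each arm has m ambiguous events of equal true relatedness, and they are labelled related with probabilities p1 and p2, the expected false difference is m × (p1 − p2). The article gives neither m nor p1 nor p2. Purely as an assumption, a gap of 0.20 with m from 10 to 60 gives 10 × 0.20 = 2 to 60 × 0.20 = 12 events. This restates the assumption and is not an estimate for this trial.

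**5. The 24 h limit (minor).** It runs from occurrence, but participants also record events and sessions are three a week on alternate days. On a fixed weekly pattern (assumed) the gaps are 48 + 48 + 72 = 168 h. The hours lying more than 24 h before the next session are 24 + 24 + 48 = 96, and 96 / 168 = 57%. This is a share of hours, not of events. Needling reactions are likely to cluster at sessions, and participants may report between visits. It shows only that some participant-recorded events could miss the limit through no fault of the team.

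**The case against.** Three stronger readings are tempting, and the article does not support them.

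- **Acupuncturists judge their own work alone.** Section 2.10 requires them to consult experts. It says only the acupuncturist; that this is the person who treated the participant is a natural reading but is not stated.
- **The trial's safety conclusion rests on this classification.** No analysis by relatedness is specified. The one stated measure counts all events, and participants and outcome assessors, who are blinded, also record them. Ascertainment and the all-event rate therefore do not depend on the label.
- **The plan flatly contradicts itself.** The text on separation and independent data collection is general and does not mention AE causality. This is a tension to reconcile.

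It can also be said that the identity and blinding of the experts is detail that an article leaves to the full protocol. That is fair as far as it goes, and their absence from the text is not the complaint. The complaint is about a rule that is stated: the acupuncturist is the classifier of every event.

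Two objections to possible remedies also stand. Hiding the needle sites from the classifier would remove evidence needed to judge causality, such as whether a skin reaction lies at a treated point. The article also does not show that the DSMB has the membership or capacity to adjudicate single cases.

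Finally, several of the AEs listed in 2.10 are local or procedural and leave less room for judgement. That limits the problem to the ambiguous remainder, including the open category of other discomforts.

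**Conclusion.** The point holds in limited form. A stated rule puts the lead in causal attribution of every AE with the one role that 2.7 says cannot be blinded, at odds with the team separation the Discussion offers as a safeguard. The consequence is confined to the related/unrelated split, which is open to differential attribution in an unknown direction. The all-event rate per session is unaffected.

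The size cannot be given, because the article contains no AE counts or labelling rates. The conclusion assumes only that some events will be ambiguous and that the split will be compared between arms. The 24 h limit is a minor point of drafting.

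**What to change.** Reword section 2.10 as follows.

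1. The acupuncturist records and describes the event but does not make the classification used for reporting.
2. That classification is made by the experts already consulted, or by another existing role independent of delivery. They are kept unaware of the arm where the event allows, and they have the final say in a disagreement. Randomisation personnel and data monitors would not suit, because 2.7 gives them access to allocations.
3. The between-arm safety comparison rests on all AEs by arm, with the relatedness split as supportive. The existing events-per-session rate already fits this.
4. Minor: the 24 h limit for classification runs from when the study team becomes aware of the event, and both the onset and awareness dates are recorded.

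The cost is a rewording, two date fields and a short arm-masked description of each event. The sample size does not change, since it is set by the PSQI. The downside is that some events, such as haematoma, reveal the arm by their nature, so masking will be incomplete and should be reported as such.

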### Trial objective

2.1

This trial aims to rigorously evaluate the efficacy and safety of EA in the treatment of insomnia disorder among older adults.

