### Sample size calculation

2.6

The sample size was determined based on the primary outcome: change in PSQI score from baseline to Week 8. A superiority trial design employing a two-sample mean comparison was used to assess whether EA demonstrates clinically meaningful superiority over SEA. Based on prior reports of the minimal clinically important difference (MCID) for PSQI in traditional Chinese medicine trials (1.69–1.80) (43, 44), the superiority margin(*δ*) was set at 1.8. The sample size per group (n) was calculated using the formula (45):

$$n=[{\left(z_{1-\alpha }+z_{1-\beta }\right)}^{2}\sigma^{2}(1+1/K)]/{\left(\in -\delta \right)}^{2}.$$

where: n is the sample size of per group, σ is the estimated standard deviation, ϵ is the difference between treatment and control group, δ is the superiority margin.

Based on a prior single-centre RCT, PSQI scores decreased by 5.67 in the EA group and 1.83 in the SEA group, yielding ϵ = 3.8 (33). Therefore, we set ϵ = 3.8, assumed a standard deviation σ = 4, a one-sided significance level α = 0.025 (z_1 − α_ = 1.960), a type II error *β* = 0.1 (z_1 − β_ = 1.282), and an allocation ratio K = 1 (1:1 allocation between the experimental and control groups).

The calculated sample size per group is n = 85. Accounting for a 20% attrition rate, the final sample size is adjusted to 107 participants per group, resulting in a total enrolment target of 214 older adults with insomnia disorder.

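### The only AE measure stated, events per intervention session, is labelled incidence and cannot show how many participants were harmed

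*Protocol article*

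**What the plan says.** Section 2.1 of the protocol article makes safety part of the trial's aim: "This trial aims to rigorously evaluate the efficacy and safety of EA in the treatment of insomnia disorder among older adults".

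Section 2.10 sets the scope of AE recording widely. It begins "Throughout the trial, adverse events (AEs) will be monitored and recorded by participants, outcome assessors, and acupuncturists", has each event classified as related to the intervention or not, and adds: "Clinically significant abnormalities in vital signs or laboratory findings will also be recorded as AEs". It then fixes the summary measure: "The incidence of AEs will be reported as the ratio of the total number of events to the total number of intervention sessions". The sentence does not say whether the ratio is calculated by arm.

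The denominator follows from section 2.8: "Participants in both groups will receive 24 intervention sessions (30 min each), administered three times per week on alternate days over 8 weeks".

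No other AE summary appears. Section 2.12 has a general rule of frequencies and percentages for categorical variables but does not mention AEs. By contrast, section 2.9.2.6 specifies a share of participants in each group for hypnotic use.

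**The concern.** Incidence is ordinarily read as the share of people affected. Events per session is something else: the average number of events per procedure. There are two problems with making it the sole stated measure.

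- **It cannot be converted to people.** Several events in one participant count the same as single events in several participants, so the number harmed cannot be recovered from the ratio.
- **The denominator does not fit all of the numerator.** A session is a sensible unit of risk for needling pain or a haematoma. It is not one for an unrelated illness or an abnormal laboratory value. In addition, section 2.2 describes 20 weeks of observation with sessions only in the first 8. Table 1 marks AEs only up to week 8, but if the words of section 2.10 on the whole trial are taken literally, follow-up events enter the numerator with no sessions to match.

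At stake is the safety half of the objective, in participants aged 60 to 85. A reader shown an AE incidence near 1% could take it that about 1 participant in 100 was affected, when the true share could be above 20%.

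**Working it through.** **Inputs from the article**

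- Sessions per participant: 24 in both arms (section 2.8).
- Participants per arm: 107, allowing for 20% attrition (section 2.6).
- AE counts: none are given. All counts below are assumptions, chosen to show the range.

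**Reproducing the plan's own figure.** With a difference of 3.8, a margin of 1.8 and an SD of 4:

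n = (1.960 + 1.282)² × 4² × 2 / (3.8 − 1.8)² = 84.08, rounded up to 85.

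85 / 0.8 = 106.25, rounded up to 107 per arm and 214 in total. This agrees with section 2.6, and the AE point does not affect it.

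**Relation between the two measures.** Let N be participants in an arm, A participants with at least one AE, and E events.

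- Stated ratio under full attendance = E / (24 × N)
- Participant risk = A / N
- Participant risk / stated ratio = 24 × A / E

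Each affected participant has at least one event, so A / E is at most 1 and the factor is at most 24. It falls as events recur in the same people, and reaches 1 when affected participants average 24 events each.

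**Same ratio, different numbers harmed.** Sessions per arm = 107 × 24 = 2,568. Assume 24 events in one arm. The stated ratio is always 24 / 2,568 = 0.93%.

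| Participants affected | Events each | Participant risk | Factor |
|---|---|---|---|
| 24 | 1 | 24/107 = 22.4% | 24 |
| 12 | 2 | 12/107 = 11.2% | 12 |
| 8 | 3 | 8/107 = 7.5% | 8 |
| 1 | 24 | 1/107 = 0.93% | 1 |

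At the extreme, if every participant had exactly one AE, the ratio would be 107 / 2,568 = 4.17% against a participant risk of 100%.

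**Effect of dropout.** Take 20% of 107 as 21 leavers and 86 completers. The article does not say when leavers stop, so assume they complete between 0 and 18 sessions on average.

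- 0 sessions: 86 × 24 = 2,064 sessions; 2,064 / 107 = 19.3 per participant
- 18 sessions: 2,064 + 21 × 18 = 2,442 sessions; 2,442 / 107 = 22.8 per participant

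The largest possible factor is then about 19 to 23 instead of 24.

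**The case against.** **The measure is legitimate.** Events per session is a recognised exposure-based rate, and it suits the events that section 2.10 lists as common, such as pain, haematoma, skin reactions and syncope. The sentence names its numerator and denominator, so a careful reader can see what it is. This stands, and it is why the rate should be kept. It does not justify the label, or the extension to events that have nothing to do with a session.

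**A condensed article need not list every safety table.** This also stands in part. A statistical analysis plan may add participant counts, and section 2.10 does not rule them out. A reader might infer that participant-level counts will not be reported at all; the article does not say that. The point rests on something narrower: the article positively defines AE incidence, and an analysis that follows that definition inherits the problem.

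**Arms can still be compared.** A reader might infer that the ratio allows no comparison between arms because events cluster within people. The documents do not support that. Both arms have the same 24 planned sessions, so event rates calculated by arm are comparable. Clustering affects the variance, and standard errors that allow for it deal with that. What the ratio cannot give is a comparison of how many participants were harmed.

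**The factor of 24 is a ceiling.** A reader might also infer a fixed 24-fold understatement. It needs one event per affected person and every session given. Recurrent minor events are plausible over 24 visits and shrink the gap, as does attrition.

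**Conclusion.** The concern holds as a fault in how a safety measure is defined. Section 2.10 labels a per-procedure event rate as incidence, applies it to every AE, and states no other AE measure. The ratio can understate the share of participants affected by a factor of 1 to 24 under full attendance, with a ceiling of about 19 to 23 if 20% drop out after 0 to 18 sessions on average. With 24 assumed events in 2,568 sessions, the same 0.93% is compatible with anything from 0.93% to 22.4% of participants affected.

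These sizes rest on assumed AE counts and an assumed timing of dropout, because the article gives neither. That the number harmed cannot be recovered from the ratio depends on neither assumption. The sample size and the primary efficacy analysis are unaffected. Nor does the point call for a different analysis set: a reader might think safety must be summarised by treatment received, but section 2.12 applies intention to treat to all analyses, and nothing here requires departing from that.

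**What to change.** In section 2.10:

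1. Rename the ratio as AE events per intervention session, restrict it to intervention-related events, report it by arm, and present it as a supplementary rate. Any between-arm comparison of it should use standard errors that allow for clustering within participants.
2. Make the main safety summary the number and percentage of participants in each arm with at least one AE, at least one intervention-related AE, and any serious AE, with the between-arm risk difference and its 95% confidence interval.

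The cost is a change of wording and slightly more tabulation. Events are already to be recorded on a form and classified by relatedness, so participant counts should be derivable without extra visits or a larger sample. The article does not say whether the form also marks events as serious, and that should be checked. The other downside is presentational: the reported AE figure is likely to look less favourable than a per-session ratio.
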